## Abstract

**Background:**

In line with a rapidly ageing global population, the rise in the frequency of falls will lead to increased healthcare and social care costs. This study will be one of the few randomized controlled trials evaluating a multifaceted falls intervention in a low-middle income, culturally-diverse older Asian community. The primary objective of our paper is to evaluate whether individually tailored multifactorial interventions will successfully reduce the number of falls among older adults.

**Methods:**

Three hundred community-dwelling older Malaysian adults with a history of (i) two or more falls, or (ii) one injurious fall in the past 12 months will be recruited. Baseline assessment will include cardiovascular, frailty, fracture risk, psychological factors, gait and balance, activities of daily living and visual assessments. Fallers will be randomized into 2 groups: to receive tailored multifactorial interventions (intervention group); or given lifestyle advice with continued conventional care (control group). Multifactorial interventions will target 6 specific risk factors. All participants will be re-assessed after 12 months. The primary outcome measure will be fall recurrence, measured with monthly falls diaries. Secondary outcomes include falls risk factors; and psychological measures including fear of falling, and quality of life.

**Discussion:**

Previous studies evaluating multifactorial interventions in falls have reported variable outcomes. Given likely cultural, personal, lifestyle and health service differences in Asian countries, it is vital that individually-tailored multifaceted interventions are evaluated in an Asian population to determine applicability of these interventions in our setting. If successful, these approaches have the potential for widespread application in geriatric healthcare services, will reduce the projected escalation of falls and fall-related injuries, and improve the quality of life of our older community.

**Trial registration:**

ISRCTN11674947

## Background

According to the United Nations’ worldwide statistics for the year 2009, the percentage of individuals aged 60 years and over will increase from 11% to 22% by 2050
[1]. In comparison to global numbers, Malaysia is expected to have an ageing society by 2035, where the population size of people aged 60 years and over will reach 44.11 million, 15% of the total population size
[2]. Falls as a cause of death in Malaysia is ranked 150 in the world, compared to 80 in the United States of America and 4 (critical) in Thailand
[3]. In developed countries, approximately 32% older people will fall within one year, where 20% of fallers will need medical attention, and less than one in ten cases result in a fracture
[4-6]. Growth of the older population is expected to be associated with an increase in number fallers presented to health care services, which will incur higher health care and social care costs, unless effective interventions can be implemented widely.

A fall has been defined by the Prevention of Falls Network Europe Consensus as, “an unexpected event in which the participants come to rest on the ground, floor, or lower level”
[7]. This broad definition has been adopted for the present study from the Kellogg’s International Working Group’s report in 1987, as our study will include falls that have occurred as a result of dizziness, syncope and cardiovascular abnormalities
[8,9].

Published data on falls in older people from Malaysia is scarce. One Malaysian study suggested that injuries sustained from falls in older people are highly prevalent, constituting 40-60% of falls cases
[10]. Previous studies have also identified the occurrence of ‘post-fall syndrome’ in fallers. Individuals who have a fear of falling appear to enter a debilitating spiral of loss of confidence, functional decline and social deprivation, physical frailty, falls, and loss of independence
[11,12]. Hypothermia, pressure-related injuries and infections may also result from falls
[13].

Falls is not a part of the natural ageing process. They are often the result of a collective and individualized set of risk factors
[9,14]. The total count of possible risk factors contributing to falls exceeds 400, among the many are impaired sensorimotor functioning, cardiovascular complications, muscle weakness, environmental factors, osteoarthritis, visual limitations and depression
[15,16]. Falls are multifactorial, the culmination of various combinations of intrinsic and extrinsic factors
[6]. Thus, assessment of fallers needs to be multifaceted, to identify potentially modifiable risk factors that could be addressed in order to reduce the overall falls risk. A recent Cochrane review has identified that multifactorial interventions are effective in reducing falls
[5].

Majority of randomized controlled trials in falls prevention were focused in developed, Western nations. In developing countries like Malaysia, the concept of ‘geriatrics’ is still at its infancy. As a result, there are few structured geriatric support services. Falls research is also under developed in Malaysia. Falls risk factors have been shown to be dependent on cultural differences and living conditions of the elderly
[17]. So, interventional approaches previously shown to be effective in developed countries may not be effective in a developing community setting. A recent Cochrane review concluded that “these are complex interventions, and their effectiveness may be dependent on factors yet to be determined”
[5]. Therefore, this study will be among the first few multifactorial falls intervention studies in an Asian community. Our main objective is to evaluate the effectiveness of an individually-tailored multifactorial intervention in reducing falls among the at risk older population in Malaysia.

## Methods/Design

### Trial design

This study is a pragmatic single-blind (assessor) randomized controlled trial of an individually-tailored multifactorial intervention for older Malaysian fallers. The study will be aptly named the Malaysian Falls Assessment and Intervention Trial (MyFAIT). The CONSORT statement is used as a guideline to design the flow of participants’ progress through the study (see attached Figure 
1).

**Figure 1 F1:**
[figure not shown]
The Malaysian Falls and Intervention Trial (MyFAIT) flowchart.

### Ethics approval

This study has received ethics committee approval from the University of Malaya Medical Ethics Committee. All potential participants will be provided with a plain language statement, and a detailed explanation of what participation in the study involves. Written consent will be taken from all individuals who agree to be involved in the study.

### Participant recruitment and randomization

The inclusion criteria will consist of participants who satisfy two criteria: (i) being aged 65 years or older with (ii) a history of two or more falls, or one injurious fall in the past 12 months. Injuries will be classified according to the International Classification of Diseases, 10th Edition (ICD-10)
[7]. Participants will be excluded if they have at least one of the following: (i) clinically diagnosed dementia (ICD-10 definition), (ii) severe physical disabilities (i.e. unable to walk with a walking aid), or (iii) major psychiatric illnesses, psychosis (i.e. schizophrenia, paranoia) or brain damage. The study will be conducted in University Malaya Medical Centre (UMMC), Kuala Lumpur, Malaysia. Three hundred urban-dwelling older adult fallers will be recruited from the primary care unit, geriatric clinic, the accident & emergency department and through referral from other specialties.

### Baseline assessment

All participants will receive a baseline assessment in the hospital’s geriatric facilities, prior to randomization (i.e. assessment will be blind to group allocation). Assessors will be by the research team consisting of geriatricians, psychiatrists, ophthalmologist, physiotherapist and researchers who have received training in administration of all assessment items. Data will be collected on falls history, comorbidities, medication history, functional ability, psychological and socio-demographic status. On average, the baseline assessment is expected to last 2 hours per participant. Nutritional health data will not be collected.

#### Physical strength and balance performance

##### Hand-grip strength

This is measured using a Jamar dynamometer with the participant seated upright and elbow flexed at 90°. Measurements will be repeated three times in each hand, and the average of the three trials will be used for analysis. Grip strength is a key prognostic indicator of clinical and functional performance caused by underlying diseases
[18,19].

##### Functional reach

The participant will be asked to stand with feet together, with the dominant arm positioned in 90° flexion. The participant will be asked to reach forwards as far as they can without overbalancing. The maximum distance reached is recorded. Shoes will be kept on for this test. Functional Reach has been shown to be able to detect balance disorders and identify change in balance performance over time
[20].

##### Timed Up-and-Go (TUG)

The is the time taken for participants to stand from a 46 cm-high chair with arms, walk forwards 3 meters at regular walking pace, turn back, and return to the original sitting position with their back against the back of the chair. This will be recorded in seconds. Shoes will be kept on for this test. Participants will be allowed to use their usual indoor/outdoor walking aid to perform this test. A meta-analysis of TUG has shown this test to have moderate discriminative capacity in distinguishing fallers from the non-fallers
[21,22].

#### Visual assessment

(i) Visual acuity, (ii) Contrast sensitivity, and (iii) Binocular vision test will be conducted using standardized methods utilizing the Snellen chart, Pelli-Robson charts and Frisby Stereotest (Near) respectively
[23-25].

#### Baseline cardiovascular assessment

A baseline resting 12-lead electrocardiogram (ECG) will be recorded. Postural blood pressure will be recorded using non-invasive continuous blood pressure monitoring device (Portapres®, Finapres Medical Systems). Following 10 minutes of rest in a supine position, participants will be asked to stand for three minutes. Orthostatic hypotension will be diagnosed if a reduction in systolic blood pressure of ≥20 mmHg, or diastolic blood pressure of ≥10 mmHg within three minutes of standing is observed
[26,27].

#### Psychological and quality-of-life assessments

These will be assessed using psychometric questionnaires: Stress, anxiety and depression will be assessed using the 21-item Depression Anxiety Stress Scale (DASS-21)
[28], quality of life will be assessed using the CASP-19
[29], and fear of falling will be assessed using the 7-item short Falls Efficacy Scale-International (FES-I)
[30]. All these questionnaires have items on 4-point Likert scales, and have been shown to be reliable and valid in older populations
[31-33].

### Randomization

The 300 fallers will be randomized to either the intervention or the control group. A computer-generated random number sequence will be created by an independent investigator. Treatment allocation will be concealed in sealed, opaque envelopes and stored in a secure location. To prevent bias, 1 year follow-up assessors will be blind to group allocation. And data analysis will be undertaken by a statistician who is blind to group allocation.

#### Control group

The control group will be provided with health advice and will continue to receive usual care by their medical practitioner and other health professionals.

#### Intervention group

Participants randomized to the intervention group will be prescribed individualized treatment programs by a medical specialist. The prescribed treatment will target six specific treatment modalities: falls education, exercise intervention, home hazards intervention, cardiovascular intervention, visual intervention, and medication review. All participants of the intervention arm will receive falls education. The decision for the Otago exercises, home hazards assessment and visual intervention will be made according to predefined criteria. Decisions for detailed cardiovascular evaluation and medication review will be based on clinical decisions made according to specific features in the participants’ clinical and medical history.

##### Falls education

An information leaflet will be sent to all individuals randomized to the intervention group. The leaflet will contain information about common risk factors and simple falls prevention strategies. It serves to increase awareness, and as a reinforcement tool on the risk factors for falls and the potential benefits of various interventions, based on the findings of previous research.

##### Otago exercise program

Participants will be referred for physiotherapy if their Timed Up-and-Go (TUG) score is 13.5 seconds or above
[21]; or if they have a clinically apparent gait and balance disorder. An individually-tailored home exercise program will be prescribed based on a modified Otago exercise program, which has been shown to be highly effective in reducing injurious fall rates among those who have a previous history of fall
[34]. The program focuses on balance and strengthening exercises of 5–8 hospital exercise sessions, with recommended home practice of at least 5 times a week. The participant will be invited to attend the hospital exercise sessions every month for three months where the intensity of the exercises will be increased as appropriate, and also to motivate ongoing participation. This is followed by recommendations for engagement in other regular physical exercises like Tai Chi, which have been shown to reduce falls
[35].

##### Home environment modifications

Participants will be referred for occupational therapy if their fall occurred at home and is non-syncopal in nature. The Home Falls and Accident Screening Tool (HOME FAST) will be administered by a trained occupational therapist to systematically detect home environmental hazards and activities in the home that could potentially increase an individual’s risk of falling
[36]. Appropriate modifications will then be recommended. To facilitate immediate implementation, equipment will be provided and installed upon completion of environmental assessment with the home owner’s consent. A second home visit will be conducted to review and encourage usage of modifications and equipment.

##### Cardiovascular intervention

Participants with a history of unexplained falls or falls associated with symptoms of dizziness, presyncope or syncope will be further investigated with cardiovascular investigations. These will include ambulatory ECG monitoring, transthoracic echocardiography, carotid sinus massage or head-up tilt-table tests or cardiac stress tests according to the history provided
[37]. If hypotensive disorders of orthostatic hypotension, vasovagal syncope or vasodepressor carotid sinus hypersensitivity are confirmed, participants will be treated with conservative advice, withdrawal of culprit medication and pharmacological interventions with vasopressors according to clinical severity. A referral for permanent pacemaker insertion or other cardiac interventions will be provided if necessary
[38].

##### Visual interventions

For individuals with a visual acuity of 6/12 or worse in either eye, the participant will be referred to the hospital’s ophthalmologist for further assessment. These will also include additional assessments for refraction errors, cataracts, retinal disorders and glaucoma. Interventions such as prescription or revision of eye glasses, cataract surgery and glaucoma treatment will be prescribed according to clinical indication.

##### Withdrawal and review of culprit medications

Following a detailed medication history, falls-risk increasing drugs (FRID) in older adults will be reviewed and withdrawn if needed. The withdrawal of potential culprit medications will be performed by the study’s geriatrician
[39].

### Outcome assessment

The primary outcome measure is the proportion of fallers between the intervention and control groups, while the secondary outcome measure is the rate of falls between the two groups.

Falls diaries with daily entries will be used to record falls occurrences, and will be returned monthly for one year from randomization, as recommended by previous studies
[7]. These diaries are written in the three main languages of Malaysia; Malay, English and Mandarin, due to varying cultural and educational backgrounds. Prompts will be provided in the falls diaries, which include how and when a fall occurred, or if there were injuries sustained after their fall. Participants will be contacted every 2 months by telephone calls to encourage complete diary returns. The participant will be followed-up for one year, and then invited back for a re-assessment using the same baseline parameters. Adherence to interventions will be recorded for sub-analysis.

Additional secondary outcomes will include changes in ECG, postural blood pressure, visual, physical and psychometric assessments from the baseline assessment to one year follow-up.

### Statistical analysis and power calculation

One hundred and thirty three participants per group (n = 266) will provide an 80% power (α = 0.05) to detect a 40% reduction in the number of individuals who experience falls, assuming that without intervention, 50% of individuals will experience a subsequent fall (based on previous studies of high risk populations)
[40,41], and a 30% drop out rate (accounting for a likely high mortality and morbidity in our participants).

All analysis will be performed on an intention-to-treat basis with the exception of those who have withdrawn or died. Missing data imputations will be performed on variables with high probability of missingness, either by discarding or replacing data with the mean of the observed values for that variable. Fall and injury rates will be assessed using negative binomial model and multiple regression. For secondary outcomes, comparisons will be conducted between the intervention and control groups. Changes within groups from baseline and potential covariates will be examined with multiple regression and paired t-test for normally-distributed continuous data and Kruskall-Wallis for skewed continuous data.

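### The analysis labelled intention-to-treat excludes everyone who withdrew or died, so it is a completers analysis that discards recorded falls

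*Protocol article*

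**What the plan says.** The analysis population is fixed in one sentence of the Protocol article, under Statistical analysis and power calculation: "All analysis will be performed on an intention-to-treat basis with the exception of those who have withdrawn or died". It governs every analysis, so it includes the primary outcome, which the Outcome assessment section defines as the proportion of fallers in each group.

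The same section sizes the trial as follows: "One hundred and thirty three participants per group (n = 266) will provide an 80% power (α = 0.05"). It takes a 50% control risk and a 40% relative reduction, and allows for "a 30% drop out rate (accounting for a likely high mortality and morbidity in our participants"). The Randomization section gives the number to be allocated as 300.

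Falls are recorded in diaries with daily entries that "will be returned monthly for one year from randomization", supported by telephone contact every two months. The only rule for missing data is to discard them or substitute the observed mean. No other section retains data from people who leave or die.

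**The concern.** The sentence contradicts itself. Intention-to-treat keeps participants in the group to which they were allocated whatever happens later. Withdrawal and death both happen after randomisation, so excluding people on those grounds leaves a completers analysis, and randomisation no longer guarantees that the compared groups are alike.

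Two features of this trial give the point weight. First, the protocol itself expects substantial loss and links it to mortality and morbidity, which are plausibly related to falling. Second, the primary event is collected month by month. Someone who returns a diary with a fall in month 3 and withdraws in month 8 has already had the primary event, as has someone who dies from a fall. The rule removes both from numerator and denominator.

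**Working it through.** **1. Reproduce the plan's sample size.** Inputs, all from the power paragraph: control risk 0.50; intervention risk 0.50 × (1 − 0.40) = 0.30; α = 0.05, taken as two-sided; power 80%; dropout 30%. With pooled variance under the null and no continuity correction:

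n = [1.96·√(2·0.4·0.6) + 0.8416·√(0.5·0.5 + 0.3·0.7)]² / 0.20² = (1.358 + 0.571)² / 0.04 ≈ 93 per group.

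93 / 0.70 = 132.9, so 133 per group and 266 in total. The stated figure is reproduced exactly. The calculation therefore already counts on only about 93 of each 133 contributing.

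**2. How many could be removed.** If the whole allowance were withdrawal or death: 0.30 × 266 ≈ 80, or 0.30 × 300 = 90. With 150 per arm, 150 × 0.70 = 105 per arm would be analysed.

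**3. Recorded falls deleted.** Assume that leavers exit uniformly over the year, that exit is unrelated to falling, and that fall counts are negative binomial with a 50% chance of at least one fall in 12 months. With dispersion 1, the chance of no fall by time t (in years) is 1/(1 + t). The chance of a fall before exit is then ∫₀¹ [1 − 1/(1 + t)] dt = 1 − ln 2 = 0.31. Dispersion 0.5 gives 0.29 and dispersion 2 gives 0.33. At about 30% of 90 leavers, some 27 of 300 participants would have a recorded fall deleted.

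**4. Possible bias.** The exit rates here are assumptions; the document gives none. Take a true 12-month risk p = 0.5 in both arms and 30% exit in each, with control exit unrelated to falling. If a fraction w_f of intervention-arm fallers and w_n of non-fallers leave, the analysed risk is

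p(1 − w_f) / [p(1 − w_f) + (1 − p)(1 − w_n)].

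For 40%/20%: 0.5·0.6 / (0.5·0.6 + 0.5·0.8) = 0.30/0.70 = 42.9%. At 105 per arm the difference is 0.0714, with standard error 0.0688 under the null and 0.0687 under these risks. Rejection in favour of the intervention is Φ[(0.0714 − 1.96·0.0688)/0.0687] = Φ(−0.92) ≈ 0.178. The other tail adds about 0.001.

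| Exit, fallers/non-fallers (intervention arm) | Analysed risk v 50% | RR | Two-sided rejection, 105 per arm |
|---|---|---|---|
| 30%/30% | 50.0% | 1.00 | 5% |
| 35%/25% | 46.4% | 0.93 | about 8% |
| 40%/20% | 42.9% | 0.86 | about 18% |
| 45%/15% | 39.3% | 0.79 | about 34% |

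**5. The other direction.** Let the true risks be 50% v 30% and put the informative exit in the control arm instead. At 105 per arm, power falls from 84.6% to about 69%, 49% and 29% for the same three patterns. At 93 per arm it falls from 80% to about 64%, 44% and 26%.

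**6. What using diary data up to exit recovers.** The no-effect scenario was simulated with dispersion 1 and uniform exit, estimating the 12-month risk by time to first fall with leavers censored. The estimate is 46.9% for 40%/20% and 45.5% for 45%/15%. The share of bias removed is (46.9 − 42.9)/(50 − 42.9) = 56% and (45.5 − 39.3)/(50 − 39.3) = 58%. The remainder comes from falls after exit that nobody observes.

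**The case against.** The strongest reply is that the rule may do little harm. If exit is equal in the two arms and unrelated to falling, the analysed proportions are unbiased, and the sample size already pays for the lost numbers. That is correct, and the sample size is not in error. But the protocol gives no ground for assuming such exit, and recorded primary events are deleted even then.

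Several stronger readings are tempting and are not supported:

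- A reader might infer that 30% of participants will be excluded. The figure is a planning allowance for dropout. Someone who stops returning diaries or misses the final visit need not have withdrawn or died, so the 80 and 90 are upper figures.
- A reader might infer that the intervention arm carries a uniformly heavier burden and so will lose more people. Only falls education goes to everyone in that arm; the other components depend on criteria or clinical judgement. Differential exit is possible, but the document offers no evidence of it.
- A reader might infer a false benefit. The table in the working shows one assumed direction only, and the opposite pattern hides a real effect.
- A reader might charge the whole of the illustrated bias to this clause. About 40% of it in the two stronger cases would survive removal of the clause.
- The 27 of 300 assumes exit unrelated to falling, so it cannot be combined with the informative-exit rows of the table.

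It is also fair to say that an unseen full protocol or SAP may hold details such as offsets or competing events, and their absence from an article is no finding. That does not help here, because the exclusion is stated outright.

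**Conclusion.** The point holds. The sentence specifies a completers analysis under an intention-to-treat label, applies it to the primary outcome, and is not corrected elsewhere in the article. Two consequences follow from the text alone: randomised participants are removed for post-randomisation events, and people already known to have fallen, or killed by a fall, are dropped. The scale is up to about 80 of 266 or 90 of 300 participants.

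The size and direction of any bias are not determined by the document. Under the stated assumptions it ranges from none to an apparent risk ratio of 0.79 with no true effect, and the same mechanism can mask a true effect. Because the rule defines the primary analysis population, it should be corrected before the data are analysed.

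**What to change.** Delete the closing exception from the sentence and state that all randomised participants are analysed as allocated, using all diary data up to withdrawal, death or 12 months. To carry this through:

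- Count anyone with a recorded or fatal fall as a faller.
- Estimate the 12-month risk by time to first fall, with death as a competing event.
- Use observed time as the offset in the negative binomial model that is already planned.
- Add a sensitivity analysis for informative withdrawal, for example by varying the assumed fall risk of leavers after exit separately by arm. This is needed because diary data up to exit do not remove all of the possible bias.
- Keep the completers analysis only as a labelled secondary analysis.

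The cost is one paragraph of wording and a little extra analysis. The diaries already exist, so no new data collection is required.

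### Replacing missing outcome values by the observed mean would shrink the treatment difference or understate its standard error, and the plan gives no criterion for choosing it over discarding

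*Protocol article*

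**What the plan says.** The section Statistical analysis and power calculation sets the rule. Its scope is broad: "Missing data imputations will be performed on variables with high probability of missingness". Two methods are offered, "either by discarding or replacing data with the mean of the observed values for that variable". Nothing says when each applies, whether the mean is taken over all participants or within arm, or whether the rule is confined to baseline or continuous variables.

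The sentence before it defines the analysis set: "All analysis will be performed on an intention-to-treat basis with the exception of those who have withdrawn or died". The same section plans for 30% dropout, which it links to expected death and illness.

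The endpoints are set under Outcome assessment. The main one is a yes/no measure: "The primary outcome measure is the proportion of fallers between the intervention and control groups". How often participants fall comes second, as a rate compared between the arms. Further secondary outcomes are changes to one year in ECG, postural blood pressure, visual, physical and psychometric measures. For falls, "Fall and injury rates will be assessed using negative binomial model and multiple regression".

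**The concern.** Baseline is assessed before randomization, whereas the re-assessment comes a year later in a population expected to be ill. The variables most likely to be missing are therefore 12-month outcomes: Timed Up-and-Go, grip strength, fear of falling, DASS-21, CASP-19 and blood pressure. Single mean replacement treats filled-in values as observed and ignores each participant's baseline.

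The harm depends on which mean is used. The overall mean gives every missing participant the same value in both arms, so those participants contribute no treatment difference. The arm mean keeps the difference but adds values with no spread, so the standard error is too small. Either way a reported effect or its confidence interval would be wrong. With no criterion fixed, the choice between methods could also be made late.

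**Working it through.** **Inputs.** From Statistical analysis and power calculation: 133 per group, 50% fallers in the control group, a 40% relative reduction (so 50% × 0.6 = 30% with intervention), alpha 0.05, 80% power, 30% dropout. Two-sided testing is assumed because the article does not state it. The fraction missing among participants kept in the analysis, f, is not given; I take 10%, 20% and 30%, equal in both arms and missing completely at random.

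**The plan's own figure.** For two proportions with pooled variance under the null, n = [1.96·√(2·0.4·0.6) + 0.842·√(0.5·0.5 + 0.3·0.7)]² / 0.2² = (1.358 + 0.571)² / 0.04 ≈ 93 per group. Then 93 / 0.7 = 132.9, so 133. The stated size reproduces and is not in dispute.

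**Overall mean.** If g is the mean of all observed values and m the observed mean in an arm, the arm's filled-in mean is (1−f)·m + f·g. Subtracting the arms, f·g cancels and leaves (1−f) times the true difference. The reported standard error shrinks by about the same factor, so the test statistic hardly moves. At f = 0.3: 0.140 / 0.049 ≈ 2.86, against 0.200 / 0.070 ≈ 2.86 for complete cases. The test keeps its size, but the estimate is too small and its interval is centred in the wrong place.

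**Arm mean.** The difference is unchanged. With s the outcome's standard deviation and n participants per arm, the reported SE is s·√(2(1−f)/n) and the true SE is s·√(2/((1−f)n)). Their ratio is 1−f. Type I error is 2[1 − Φ(1.96·(1−f))]:
- f = 0.1: 2[1 − Φ(1.764)] = 7.8%
- f = 0.2: 2[1 − Φ(1.568)] = 11.7%
- f = 0.3: 2[1 − Φ(1.372)] = 17.0%

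**Simulation check.** 10,000 trials per scenario, 133 per arm, true difference 20 points (or none, for type I error):

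| Missing | Overall mean: estimate | Overall mean: type I error | Arm mean: estimate | Arm mean: reported SE / true SE | Arm mean: type I error | Discarding: estimate | Discarding: type I error |
|---|---|---|---|---|---|---|---|
| 10% | 18.0 points | 5.1% | 20.1 points | 0.056 / 0.062 | 8.2% | 20.1 points | 5.2% |
| 20% | 16.0 points | 5.1% | 20.0 points | 0.053 / 0.066 | 11.7% | 20.0 points | 5.1% |
| 30% | 14.0 points | 5.3% | 20.0 points | 0.049 / 0.070 | 17.2% | 20.0 points | 5.4% |

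At 30% missing, arm-mean replacement also shows apparent power of 93%, against 80% from complete cases.

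The yes/no outcome is used here because the article gives its planning rates. The ratios do not depend on outcome type. For a continuous measure with a true difference of 0.40 SD and 30% missing (150 per arm, 5,000 trials), overall-mean replacement gave 0.278 SD, against 0.40 × 0.7 = 0.28 expected. Arm-mean replacement rejected a true null in 17.7% of trials.

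**If applied to falls.** Under the planning rates the filled-in faller value would be 0.3 or 0.5 (arm means) or 0.4 (overall mean), where only 0 or 1 is possible. A mean fall count is generally not a whole number, which a negative binomial likelihood does not admit.

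**The case against.** Several stronger readings are tempting, and the article does not support them.

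- **That discarding does the same harm.** It does not. Under data missing completely at random it is unbiased with correct type I error. Its cost is lost precision, and possible bias if missingness relates to morbidity, which the article's own reason for dropout makes plausible.
- **That 30% of outcomes would be imputed.** The 30% is dropout attributed to death and illness, and withdrawn and deceased participants are removed from all analyses. Much of that 30% would be excluded rather than filled in, so 30% is an upper case.
- **That the plan implies 17% type I error.** The wording refers to the mean for the variable and does not mention arm, so the overall mean is the plain reading. Under that reading type I error stays near 5% with equal missingness. Shrinkage and a false standard error are alternatives; they do not occur together.
- **That the primary outcome will be mean-imputed.** The article does not say so. Monthly diaries and two-monthly telephone calls are meant to limit missing falls data.
- **That the method can freely be picked to suit the result.** Under Randomization, the article says the statistician is blind to allocation. This limits steering but does not fix the choice, since group codes alone are enough to compare the options.

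These points narrow the size and scope. They do not rescue the rule, because each form of mean replacement damages either the estimate or its interval.

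**Conclusion.** The point holds as a fault in a stated method. It is not a detail left to an unseen analysis plan, because such a plan would have to reverse the sentence. On the plain reading, the between-group difference in 12-month outcomes is understated by the fraction imputed: 10–30% over the assumed range. On the arm-mean reading, type I error is about 8–17%. These figures assume missingness that is completely at random and equal between arms. The true fraction among retained participants is unknown and probably below 30%. The consequence for the fall outcomes is conditional: the text does not exclude them from the rule, but does not include them either. The sample size stands.

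**What to change.** Delete mean replacement for outcomes and state one approach per type of outcome:

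- **12-month continuous outcomes:** analyse under missing-at-random by multiple imputation, done separately by arm and including the baseline value, with a sensitivity analysis for data not missing at random.
- **Fall rate:** no mean imputation; enter observed diary time as exposure in the negative binomial model.
- **Primary yes/no outcome:** use the observed diary data, with either a pre-stated rule or multiple imputation for participants whose diaries are incomplete.
- **Baseline covariates:** mean imputation may be kept here only.

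The number of imputations and the full covariate list can be left to the statistical analysis plan. This change does not by itself reach withdrawn or deceased participants while they remain excluded from the analysis set. The cost is revised wording and slightly more analysis work; no new data or participants are needed.
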